### Ethics and trial registration

2.4

The ethical and informed consent materials for this study protocol were approved by the Ethics Committee of the Affiliated Hospital of Nanjing University of Traditional Chinese Medicine (Jiangsu Provincial Hospital of Traditional Chinese Medicine) on June 13, 2024, with the Committee Approval No. 2024NL-124-02. The study was likewise registered in the China Clinical Trial Registry, with Approval No. ChiCTR2400085660.The study was conducted with the approval of the China Clinical Trial Registry (CCTR).

### Randomization

2.5

Following screening according to inclusion and exclusion criteria, 33 eligible patients with insomnia will be split into two groups, A and B, using whole cluster randomization, with a 1:1 ratio. Researchers not participating in the experimental implementation will create the randomized sequences and use IBM’s SPSS 25.0 software (IBM, Armonk, NY, USA) for statistical analysis. The randomized sequences will be inserted into opaque envelopes in the order of inclusion using the envelope method of concealment. Patients who fulfilled the requirements were given envelopes in the order of enrollment to be given to the data analyst, who then obtained the patient groups. An individual else was in charge of patient inclusion.

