**Methods:**

A single-center, double-blind, clinical trial was the study’s design. For this study, a total of 99 participants were enrolled, and they will be split into two groups: one for insomnia and the other for health. There are 33 healthy people in the healthy group and 66 insomnia patients in the insomnia group. Acupuncture treatment will be administered to the intervention group three times a week for four weeks, for a total of twelve treatments, and will be followed up for 3 months. A combination of UPLC-Q/TOF-MS and UPLC-QQQ-MS/MS was used to qualitatively and quantitatively examine the serum of 99 participants. The Pittsburgh Sleep Quality Index (PSQI) and serum metabolomics provided the primary findings. The Insomnia Severity Index (ISI), Hyperarousal Scale (HAS), Fatigue Feverity Scale (FSS), Hamilton Depression Scale (HAMD), Hamilton Anxiety Scale (HAMA), Sleep Diary and The Montreal Cognitive Assessment (MoCA) were the secondary outcomes. For the insomnia group, serum will be collected at baseline, at the end of treatment, and the scale will be collected at baseline, after 4 weeks of treatment, and at 3 months of follow-up. For the healthy group, serum will be collected at baseline.

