### Study design

2.1

The study design is a single-center, double-blind, clinical trial to investigate the metabolic pathways and possible mechanisms underlying the efficacy response of electroacupuncture for insomnia. The study protocol follows the SPIRIT guidelines, 99 subjects will be recruited and divided into an insomnia group and a healthy group. The International Classification of Sleep Disorders, Third Edition (ICSD-3) diagnostic criteria will be used to diagnose subjects with insomnia. Those who meet the inclusion criteria will also sign an informed consent form, complete the following scale assessments, and have their serum collected: PSQI and ISI to measure sleep; HAS to measure hyperarousal state; HAMD and HAMA to measure mental state; and FSS to measure physical and mental fatigue, sleep diary to measure sleep behavior, and MoCA to measure cognition to gather baseline assessment data. This will be followed by 4 weeks of treatment. Retesting of the above scales will be completed at the end of treatment and at 3 months follow-up, as well as serum collection’s will be completed at the end of treatment. The healthy group will complete serum collection at enrollment. The insomnia group will be randomly divided into Group A and Group B, matched with the healthy group. Group A and the healthy group will be screened for differential metabolites using metabolomics analysis with non-targeted UPLC-Q/TOF-MS, and Group B will be quantified for the screened differential metabolites using metabolomics with targeted UPLC-QQQ-MS/MS. The flow chart of the experiment is shown in **Figure 1**. The flow schedule is shown in **Figure 2**.

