### Sample size

2.3

PASS 15.0 software was used to determine the sample size based on the nature of the study, with the control group being the healthy group and the treatment group being the insomnia group. Patients with insomnia use the PSQI score as an observed outcome indicator. Based on the pre-test results and literature review, the mean PSQI score for the drug control group is 10.76 ± 3.32 points, and it is anticipated that this score will decrease by 2.63 points for the insomnia group. The effect size (Effect Size) of the two groups is 0.8, α=0.05, Power=0.9, and this means that the sample size for the treatment group is 52 cases, and the sample size for the health group is 26 cases; taking into account variables like fewer visits, an increase in cases, and an increase in cases. The sample size for the treatment group was 52 cases, and the sample size for the healthy group was 26 instances. After taking lost visitation into account, the sample size was expanded by 15%, resulting in 66 cases for the treatment group and 33 cases for the healthy group in this experiment.

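### The randomisation section allocates 33 insomnia patients by cluster, while the rest of the article has 66 patients allocated one by one

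*Protocol article*

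**What the plan says.** The rule for forming the two insomnia subgroups is in section 2.5 (Randomization): "33 eligible patients with insomnia will be split into two groups, A and B, using whole cluster randomization, with a 1:1 ratio". The same section then says: "The randomized sequences will be inserted into opaque envelopes in the order of inclusion using the envelope method of concealment". On the handling of patients it adds: "Patients who fulfilled the requirements were given envelopes in the order of enrollment".

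The other statements on numbers and on who is divided are:

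- Abstract, Methods: "There are 33 healthy people in the healthy group and 66 insomnia patients in the insomnia group".
- Section 2.3 (Sample size): "resulting in 66 cases for the treatment group and 33 cases for the healthy group in this experiment".
- Section 2.1 (Study design): "99 subjects will be recruited and divided into an insomnia group and a healthy group".
- Section 2.1 again: "The insomnia group will be randomly divided into Group A and Group B, matched with the healthy group".

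Section 2.1 also describes the setting: "The study design is a single-center, double-blind, clinical trial". It gives the subgroups their roles. Group A is compared with the healthy group by untargeted metabolomics to find differential metabolites, and Group B is used to quantify those metabolites by the targeted method. Section 2.6 (Blinding) confirms that the acupuncture protocol is the same throughout the insomnia group.

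**The concern.** Two things in one sentence do not fit.

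The first is the number. If 33 insomnia patients are randomised, either half of the 66 have no group or the trial is smaller than the 99 people stated.

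The second is the method. Cluster randomisation allocates intact groups of people. Here patients are enrolled singly at one centre, no cluster is defined anywhere, and the envelope procedure allocates patient by patient. Someone preparing the list cannot follow both descriptions.

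Metabolomics is named as a primary outcome alongside PSQI, and the Discussion rests the reliability of the markers on the two techniques validating each other. That argument needs a discovery set of the intended size, and it needs A and B to be comparable samples of the same insomnia population. Individual random allocation of all 66 patients provides this. An allocation of 33 patients in undefined blocks would not be known to provide it.

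**Working it through.** **1. The article's own sample size.** Inputs from section 2.3: effect size 0.8, alpha 0.05 (two-sided assumed, since sidedness is not stated), power 0.90, insomnia to healthy 2:1. A two-sample t-test gives 25.3 healthy, rounded up to 26, and 2 x 26 = 52 insomnia. This matches the stated 52 and 26. The article then gives 66 and 33 after allowing for loss. Those two figures are larger than a 15% allowance yields (52/0.85 = 61.2, so 62; 26/0.85 = 30.6, so 31). That is a separate matter: 66 is the insomnia total in both places where the article states that total.

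**2. The numbers side by side.**

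| Place | Insomnia patients | Total |
|---|---|---|
| Abstract, Methods | 66 | 99 |
| 2.1 Study design | whole insomnia group divided into A and B | 99 |
| 2.3 Sample size | 66 | 66 + 33 = 99 |
| 2.5 Randomization | 33 divided into A and B | not stated |

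A 1:1 split of 66 gives 66/2 = 33 per group, so Group A would equal the healthy group in size. A 1:1 split of 33 gives 33/2 = 16.5, that is 16 and 17. It leaves 66 - 33 = 33 insomnia patients without a group, or implies a trial of 33 + 33 = 66 people.

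**3. The method.** Section 2.5 describes envelopes filled in order of inclusion and given to patients in order of enrolment. The unit of allocation is therefore the patient. Section 2.1 has one centre. No cluster, cluster size or intracluster correlation is given.

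**4. Illustration of the literal reading.** This compares Group A with 33 healthy participants on one metabolite, by a two-sided t-test at 0.05 without multiplicity correction. The effect size d = 0.8 is borrowed from the PSQI calculation, because the article gives none for a metabolite. Power is the probability that a noncentral t with n1 + n2 - 2 degrees of freedom exceeds the critical value in absolute size. The noncentrality is d x sqrt(n1 n2/(n1 + n2)).

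| Group A v healthy | Noncentrality | Power | Effect detectable with 90% power |
|---|---|---|---|
| 33 v 33 | 0.8 x sqrt(1089/66) = 3.25 | 0.89 | 0.81 SD |
| 17 v 33 | 0.8 x sqrt(561/50) = 2.68 | 0.75 | 0.99 SD |
| 16 v 33 | 0.8 x sqrt(528/49) = 2.63 | 0.73 | 1.01 SD |

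The standard error of the difference rises by sqrt(1/16.5 + 1/33)/sqrt(1/33 + 1/33) = sqrt(1.5) = 1.22, or about 22%.

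**The case against.** The strongest reply is that the article largely corrects itself. Everything outside the one sentence points to 66 patients with 33 in each group, and the envelope procedure is plainly individual. A drafting slip, with 33 per group written as 33 in total, is the likeliest explanation. Figure 1 may print the group sizes and is not available. This stands as an account of how the error arose. It does not make the sentence right, and that sentence is the rule from which the list is built.

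Three stronger readings are tempting, and the documents support none of them.

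- *The discovery set will be halved.* This follows only if the sentence is obeyed against every other statement of size. The power figures are also not a loss against any planned power for Group A. They borrow a PSQI effect size, and section 2.9.3.2.4 screens many metabolites by VIP above 1 together with p < 0.05, not by one t-test.
- *The treatment result is biased.* A and B receive the same electroacupuncture, and no treatment comparison between them is described. The split cannot bias the PSQI result.
- *Clustering inflates the variance by a calculable amount, or makes A and B differ by recruitment source or period.* Section 2.2.1 lists three recruitment routes, but nothing says that they, or enrolment waves, serve as clusters. With no clusters, sizes or correlation in the document, any such figure would be invented.

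That 33 is odd adds little: 16 and 17 is an ordinary near-equal split.

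**Conclusion.** The point holds as an error in the randomisation rule. Section 2.5 gives a number that the Abstract and sections 2.1 and 2.3 contradict, and an allocation method that its own envelope procedure contradicts. This is not detail left to a fuller document, because the text makes two statements that cannot both be true.

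Its reach is limited to the size and comparability of the discovery set (A) and the quantification set (B). On the literal reading Group A has 16 or 17 patients instead of 33, with illustrative power of 0.73-0.75 instead of 0.89. This rests on three assumptions: a two-sided single test at 0.05, d = 0.8 carried over from PSQI, and an intended Group A of 33, which is inferred from splitting 66 equally because the available text does not print it. Whether the list actually in use has the error cannot be told from the article.

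**What to change.** Replace the sentence in section 2.5 with one saying that all 66 eligible insomnia patients are individually randomised 1:1 to Group A (33) or Group B (33), with one sealed envelope per patient in order of enrolment. Delete the words *whole cluster*. Nothing in the article calls for a particular blocking scheme, so the correction need not add one.

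Section 2.14 says that recruitment is under way, so someone independent of enrolment should check that the list in use covers 66 individual patients. If it does, the change is purely editorial and costs one sentence. If it does not, extend the list prospectively to the remaining patients, leave existing allocations as they are, and report what was done and when. That second case costs an amendment and a short account in the results paper.

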### Blinding

2.6

By the principle of blinding, the grouping results will be blinded to the participants, acupuncturists, and evaluators. Because the acupuncture protocol was consistent in the insomnia group of this study, the acupuncturists do not need to know the grouping results and the acupuncturists cannot assess the results of the intervention. This study will be blinded to the evaluators, who will not be informed of the subgroups, will only be responsible for collecting data from the subjects, and will not be allowed to discuss the treatment with the evaluators. Because the insomnia group of this graduate student will be analyzed using a different metabolomics technique, this study will not be blinded to the metabolomics technique, and data analysts, who will be asked to perform the analysis according to their assigned group will be responsible for statistical analysis and data interpretation.

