#### Healthy group

2.7.2

The healthy group will not receive any treatment.

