##### Metabolite extraction

2.9.2.1

Metabolite extraction was performed by the organic reagent protein precipitation method. Extraction method: take the cryopreserved serum samples, sorted according to the order of uptake, static thawing until completely liquid; take 40 μL of each sample and add it to the corresponding 96-well plate, add 120 μL of pre-cooled methanol, seal the membrane, shake and mix for 1 min, and place it in the refrigerator at -20 °C overnight; take it out on the next day, reconstitute the dissolution, and centrifuge it for 30 min under the condition of 4 °C, 4000 rpm, and then take 25 μL of the supernatant into a new 96-well plate, add 225 μL of 50% methanol for dilution, and then take it out on the following day. Take 25 μL of supernatant in a new 96-well plate, add 225 μL of 50% methanol for dilution, each take 60 μL of supernatant transferred to a new 96-well microtiter plate, according to the order of the uploading sequence, sealing the membrane marking, and ready for inspection. Take 20μL from each prepared sample and mix it into a prepared quality control sample (hereinafter referred to as “QC sample”).

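### The trial is called double-blind, but only the A/B assay assignment is masked; no masking of treatment, diagnosis or visit is stated for the comparisons that carry the conclusions

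*Protocol article*

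**What the plan says.** **Label.** Section 2.1: "The study design is a single-center, double-blind, clinical trial". The Abstract and the Discussion repeat the term.

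**What is masked, and from whom.** Section 2.6: "the grouping results will be blinded to the participants, acupuncturists, and evaluators". The grouping is A versus B within the insomnia group. The section explains that the acupuncturist has no need to know it: "Because the acupuncture protocol was consistent in the insomnia group of this study".

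**What A/B decides.** Only the assay. Group A is screened with the healthy group by untargeted UPLC-Q/TOF-MS, and "Group B will be quantified for the screened differential metabolites using metabolomics with targeted UPLC-QQQ-MS/MS" (section 2.1).

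**Comparator.** Section 2.7.2: "The healthy group will not receive any treatment". No sham procedure appears anywhere.

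**Analysts.** Section 2.6: "this study will not be blinded to the metabolomics technique, and data analysts, who will be asked to perform the analysis". Section 2.5 has the envelopes "given envelopes in the order of enrollment to be given to the data analyst, who then obtained the patient groups".

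**Sample order.** Section 2.9.2.1 begins extraction with: "take the cryopreserved serum samples, sorted according to the order of uptake". It later plates the extracts by an uploading sequence. Neither term is defined.

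**The concern.** Blinding helps only if it hides the contrast being tested. A and B receive the same treatment and are not compared for efficacy, so hiding that label protects no efficacy or mechanism conclusion. Two contrasts do carry the conclusions (Introduction and Discussion): insomnia versus healthy, which selects the differential metabolites, and before versus after electroacupuncture, which is to show whether they move back.

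PSQI and serum metabolomics are both primary outcomes. PSQI is a questionnaire completed by patients who know they have been treated. For metabolomics, staff who know diagnosis and visit while the data set is being assembled could influence later discretionary steps such as metabolite identification, handling of outlying samples and choice of model. An undefined run order also leaves open whether instrument drift could line up with diagnosis or visit. Selected features become the Group B panel, so an artefact that passes the screen is carried forward. A reader who sees the double-blind label will assume protections that the text does not provide.

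**Working it through.** The plan gives no figure on this point, so the main check sets the sections side by side.

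| Contrast | Stated masking | Source |
|---|---|---|
| A v B (assay only) | Hidden from participants, acupuncturist, evaluators; known to analysts | 2.1, 2.5, 2.6 |
| Treated v untreated | None possible: one regimen for all patients, no sham, healthy group untreated | 2.6, 2.7 |
| Insomnia v healthy (serum) | None described for laboratory or analysts | 2.6, 2.9 |
| Before v after (serum) | None described for laboratory or analysts | 2.6, 2.9 |
| Before v after (PSQI) | Patient knows treatment and visit; evaluator masked to A/B only | 2.6, 2.8 |

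The only masked row is the one that is not a treatment contrast. The reason given for unblinding analysts is that A and B use different assays. That requires knowing the platform for a tube. It does not require knowing, within a platform, whether the tube is from a patient or a healthy person, or from baseline or week 4.

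**Worst-case illustration of run order.** Assumptions, none from the article: linear uncorrected drift of X SD in total over 66 injections; unit variance; two-sided 5% test; 33 per group (66 patients split 1:1, and 33 healthy); all of one group run before all of the other.

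- The mean shift between the two halves is δ ≈ X/2.
- Two groups: rate ≈ 1 − Φ(1.96 − δ/√(2/33)) + Φ(−1.96 − δ/√(2/33)), with √(2/33) = 0.246.
  - X = 0.5, δ = 0.25: δ/0.246 = 1.02, rate 17.4% (simulated 17%).
  - X = 1.0, δ = 0.50: δ/0.246 = 2.03, rate 52.8% (simulated 52%).
- Paired, within-person correlation 0.5 assumed: SD of the difference = √(2(1 − 0.5)) = 1. With all baseline samples before all week-4 samples, δ√33 = 1.44 and 2.87. The normal approximation gives 30% and 82%; a simulated paired t-test gives 29% and 81%.
- Random order, two groups: about 5% at either drift.

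**Less extreme case.** Suppose samples were run in true collection order with rolling enrolment. Early patients' week-4 samples then precede later patients' baselines, and the paired shift falls. With uniform enrolment and a one-month gap between samples (recruitment length assumed), simulated paired rates for X = 0.5 and 1.0 are about:

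- 6 months: 7% and 15%
- 12 months: 5–6% and 8%
- 18 months: 5% and 7%

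So the large paired figures need fully blocked runs. Collection order alone does not produce them.

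**The case against.** **A reader might infer that samples are run in order of collection.** The article does not show this. Read with the uploading sequence in the same section, the order of uptake may be the instrument loading order, which could itself be randomised. Section 2.11 says standard operating and quality control procedures will be established for both platforms, and an article may leave run order to them. This objection stands: the point is an ambiguous term, not a shown fault. The drift figures also ignore the pooled QC sample of section 2.9.2.1, although its use for drift correction is not described.

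**A reader might infer that peak processing is subjective.** The Data preprocessing section says that noise filtering, peak identification and normalisation are automatic, so that inference fails. Some discretion may remain in later identification and modelling.

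**Analysts need labels.** PLS-DA and OPLS-DA are supervised and cannot run without class labels, and the sentence on unblinding concerns the assay technique. This is right at the modelling stage. It does not require diagnosis and visit to be known before the processed data are fixed.

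**The targeted panel is a check.** It uses different patients and another platform, so some artefacts from the screen would be caught. This stands and softens the consequence.

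**Blinded audits are mentioned in section 2.12.** They are listed among retained quality control records; that is not blinded assay or analysis.

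None of these objections supports the double-blind label.

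**Conclusion.** The point holds as a fault in what the article states about blinding. The double-blind label is unsupported: the masked A/B assignment determines only the assay, treatment is open to every patient, and analysts are unblinded and given the allocation. No masking of diagnosis or visit is described for the comparisons behind the metabolomic primary outcome, and the before/after change in PSQI is unblinded.

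The size of any resulting bias cannot be derived from the article. The 17% to 81% range is a worst case resting on assumed drift, fully blocked runs and no correction; under rolling enrolment the paired figures are about 5% to 15%. These figures are a reason to define the run order. They are not evidence that false findings will arise. The change is worth making because it is cheap and alters what section 2.6 claims.

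**What to change.** 1. **Abstract, section 2.1 and Discussion:** replace double-blind with open-label treatment, with the A/B assay assignment concealed from participants, acupuncturist and evaluators. Acknowledge that the self-reported PSQI before/after change is unblinded.
2. **Section 2.6:** give each serum tube a random code that hides diagnosis and visit from laboratory staff and analysts until the processed feature table is locked. Then release class labels for PLS-DA and OPLS-DA. The platform for each tube can remain known.
3. **Section 2.9.2.1:** replace the undefined order with a computer-generated random run order, balanced over diagnosis, with each patient's baseline and week-4 samples on the same plate in random order. If the operating procedures already do this, say so.

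Cost: one code list, relabelling and wording, with no extra patients or assays. Recruitment was under way at publication and serum is stored at −80 °C, so samples not yet assayed can still be coded and ordered this way.
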